#### Primary outcome

The primary outcome will be dietary salt intake and will be assessed at baseline and at 8, 16, and 24 weeks. For feasibility, daily salt intake will be measured using a spot morning urine sample and will be calculated using the following equation:

Daily salt intake (g/day) = 0.0585 × 21.98 × {urinary sodium (mEq/L)/urinary creatinine (mg/dL) × (14.89 × body weight (kg) + 16.14 × height (cm) – 2.04 × age (years) – 2244.45)}^0.392^ [15]. Spot morning urine samples will be collected using an immunoturbidimetric assay (Autokit Micro Albumin, Wako, Osaka, Japan).

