### Inclusion criteria

Patients will be considered for inclusion in the study if they meet all of the following inclusion criteria: willing and able to give informed consent for participation in this study; male or female, aged between 20 and 90 years old; diagnosed with T2DM (we will apply the Japan Diabetes Society’s “Committee report on classification and diagnostic criteria of diabetes mellitus” for diagnosing diabetes [11]); and salt intake ≥ 6 g per day in patients with hypertension [12], salt intake ≥ 7 g per day in female patients without hypertension, or salt intake ≥ 8 g per day in male patients without hypertension [13]. Daily salt intake will be measured using a spot morning urine sample.

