### Statistical methods

A mixed model will be used to analyze the factors involved in sodium intake. Factors and changes in factors that may influence sodium intake will be adjusted in multivariate models. Subgroup analyses will be conducted stratified by age (< 65 years or ≥ 65 years), sex (male or female), body mass index (< 22%, or ≥ 22%), and hemoglobin A1c levels (< 7%, or ≥ 7%) to investigate the coherency of educational effect among subgroups. The secondary outcomes will be compared using separate regression models. The differences of values between the two groups with 95% confidence interval and a *p* value < 0.05 will also be presented. We will use an intention-to-treat analysis. JMP version 11.2.0 software (SAS Institute, Cary, NC, USA) will be used as the statistical software package for the analysis. All analyses will be two-sided, and *p* values < 0.05 will be considered statistically significant. Multiple imputations will be applied if there are missing values. In a previous study, it was shown that after patients with T2DM were given instructions on reducing salt intake, their salt intake declined from 10.3 ± 1.6 g to 9.3 ± 1.9 g per day [10]. Therefore, we have based our sample size calculation on the assumption that the intervention group will show a 1-g reduction in their daily salt intake, and that the salt intake in the control group will remain unchanged. With the two-sided significance level set at 5.0% and power set at 80%, the required sample size will be 90 participants in each group. Assuming a 10% dropout rate [17], a total of 200 participants will be required for both groups combined.

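### The printed salt-intake equation omits the factor of 10 that converts creatinine from mg/dL to mg/L, so as written it overstates daily salt intake 2.47-fold

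*Protocol article*

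**What the plan says.** The Primary outcome section says that "daily salt intake will be measured using a spot morning urine sample and will be calculated using the following equation". The equation has three parts:

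- leading constants: "Daily salt intake (g/day) = 0.0585 × 21.98";
- inside the braces, the ratio "urinary sodium (mEq/L)/urinary creatinine (mg/dL") multiplied by the term "14.89 × body weight (kg) + 16.14 × height (cm) – 2.04 × age (years) – 2244.45";
- the exponent on the braces, 0.392.

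The units of sodium and creatinine are printed explicitly. No conversion between litres and decilitres appears.

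The Inclusion criteria section uses a measure described in the same way: "Daily salt intake will be measured using a spot morning urine sample". It applies fixed cut-offs, the lowest being "salt intake ≥ 6 g per day in patients with hypertension", with 7 g for women and 8 g for men without hypertension.

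The Statistical methods section gives the scale on which the trial was planned. In a previous study of patients with type 2 diabetes, "their salt intake declined from 10.3 ± 1.6 g to 9.3 ± 1.9 g per day", and the planned effect is a reduction of 1 g/day.

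**The concern.** Sodium is expressed per litre and creatinine per decilitre, so the volumes do not cancel. If the weight, height and age term is predicted creatinine in mg/day, the braces hold ten times the daily sodium excretion in mEq.

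If the equation were applied as printed:

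- **Eligibility.** The 6, 7 and 8 g/day cut-offs would no longer pick out excessive consumers, because almost every patient would exceed them.
- **Primary outcome.** Baseline values, follow-up values and the treatment difference in g/day would all be about 2.5 times too large, and could not be compared with the 1 g planning effect.
- **Intervention.** Both arms are told their salt intake at baseline, and the intervention arm is told again at follow-up. An inflated figure would become part of what is being tested.
- **Reuse.** The Discussion offers the protocol as guidance to other researchers, who could copy the equation as it stands.

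**Working it through.** **Inputs from the article.** Constants 0.0585 and 21.98 (product 1.2858); sodium Na in mEq/L; creatinine Cr in mg/dL; the weight, height and age term P; exponent 0.392; cut-offs of 6, 7 and 8 g/day; benchmark intakes of 10.3 and 9.3 g/day. The article gives no worked value of the equation, so there is no figure of its own to reproduce.

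**Assumed inputs.** Body size 65 kg, 165 cm, 60 years; Na 120 mEq/L and Cr 100 mg/dL; ranges of Na 60–150 and Cr 80–150.

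**1. Scale of P.**
P = 14.89 × 65 + 16.14 × 165 − 2.04 × 60 − 2244.45 = 967.85 + 2663.10 − 122.40 − 2244.45 = 1264.1.
The article does not state the unit of P. Its size is plausible only as mg/day.

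**2. Units.** Since 1 mg/dL = 10 mg/L, sodium excretion in mEq/day is Na/(10 × Cr) × P. The printed form, Na/Cr × P, is ten times this.

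**3. Effect on the result.** The braces are raised to 0.392, so the inflation is 10^0.392 = 2.466. It is the same for every patient and does not depend on the assumed values.

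**4. Worked example.**
- As printed: 1.2858 × (120/100 × 1264.1)^0.392 = 1.2858 × 1516.9^0.392 = 22.7 g/day.
- With the factor: 1.2858 × (120/1000 × 1264.1)^0.392 = 1.2858 × 151.7^0.392 = 9.2 g/day.

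**5. Range.**

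| Assumed values | As printed (g/day) | With × 10 (g/day) |
|---|---|---|
| Na 60, Cr 150; 65 kg, 165 cm, 60 y | 14.8 | 6.0 |
| Na 150, Cr 80; 65 kg, 165 cm, 60 y | 27.0 | 11.0 |
| Four body sizes (45–80 kg, 145–172 cm, 50–85 y) and six Na/Cr pairs, including Na 30 with Cr 200 | 7.5–29.8 | 3.0–12.1 |

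**6. Could the coefficient 21.98 already absorb the factor of 10?** In an empirical power-law equation it could, so the constants were tested without assuming any urine concentration. Let x be the content of the braces.
- The equation returns exactly the sodium put into it when 21.98 × x^0.392 = x, that is x = 21.98^(1/0.608) = 161. In mEq/day this is 161 × 0.0585 = 9.4 g/day, inside the article's own 9.3–10.3 g/day. The constants therefore fit braces in mEq/day.
- For the same urine, the printed form has braces of 1,610 and returns 9.4 × 2.466 = 23.3 g/day.
- To return 10.3 g/day, x must be (10.3/1.2858)^(1/0.392) = 202. With the factor this is 202 mEq/day (202 × 0.0585 = 11.8 g of salt). As printed it is only 20.2 mEq/day (1.2 g of salt). For the example patient at Cr 100 mg/dL, the urine sodium needed is about 160 mEq/L with the factor and about 16 mEq/L as printed.

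**7. Cut-offs.** On the printed scale, 6, 7 and 8 g/day correspond to 6/2.466 = 2.4, 7/2.466 = 2.8 and 8/2.466 = 3.2 g/day on the corrected scale. For the example patient at Cr 100 mg/dL, they are reached at urine sodium of about 4, 6 and 8 mEq/L as printed, against about 40, 60 and 84 mEq/L with the factor.

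**The case against.** The strongest reply is that this is a slip in copying a published formula, and that nothing shows the trial calculates with the printed version. The cut-offs, the benchmark intakes and the 1 g planned effect all sit on the corrected scale. This stands. The article cannot settle which form is in use, so distorted trial data are not shown.

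Second, the factor is constant across arms and visits. It cancels from the p value of an unadjusted comparison, from the standardised effect and from percentage change, and the sample size of 90 per group does not depend on it. This also stands. What it would change is the g/day scale, the fixed cut-offs and the intake reported to participants.

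Third, the Inclusion criteria section does not cite the equation. The link to eligibility is an inference, though a fair one: the measure is described in the same way and no other formula is given.

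Fourth, the previous study's method of measurement is not stated, and the printed form can return about 10 g/day for some inputs. Over the wider set of assumptions its range starts at 7.5 g/day. The low values arise only when the sodium-to-creatinine ratio is low (for instance Na 30 with Cr 200), most of all in small patients, and not in ordinary urine. So it is too strong to say that the printed form can never give 10 g/day, but it does not do so at ordinary concentrations.

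Fifth, units need not cancel in an empirical regression. That is true in general, but step 6 of the working shows that these constants fit braces in mEq/day and not ten times that.

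**Conclusion.** The equation is wrong as written. It lacks a factor of 10 on creatinine and so overstates daily salt intake by 10^0.392 = 2.47 for every patient. This multiplier rests on the printed units, the exponent and the reading of the weight, height and age term as mg/day, which is inferred from its size and supported by the article's own benchmark. The g/day examples rest on assumed urine and body values; the multiplier does not.

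The conclusion concerns the printed text. Whether screening, outcome values and the figures told to patients are affected depends on the calculation code, which the article does not show. Because this is the only formula for the primary outcome, and apparently for entry, it must be corrected and the code checked.

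**What to change.** Rewrite the braces as {Na (mEq/L) / [10 × Cr (mg/dL)] × (weight, height and age term)}^0.392, and state that the last term is predicted creatinine in mg/day. State in the Inclusion criteria section that the same equation is used there.

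Then check the spreadsheet or code used for screening, for outcome data and for the values told to participants. If the factor of 10 is present, a published correction of the equation is enough. If it is absent, recompute all stored values from the raw sodium and creatinine, re-check each participant against the eligibility cut-offs, and document what participants were told.

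The cost is a one-line correction and a code check. No new data are needed.

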#### Secondary outcomes

The secondary outcomes will include body weight, hemoglobin A1c, blood pressure, serum lipid profile (triglycerides and high-density lipoprotein cholesterol), estimated glomerular filtration rate, and urinary albumin excretion (UAE) [9]. Blood samples for biochemical measurements will be taken in the morning.

Hemoglobin A1c level, serum lipid profile, and other biochemical data will be determined using standard laboratory measurements. The UAE will be measured with an immunoturbidimetric assay. The hemoglobin A1c level will be expressed in National Glycohemoglobin Standardization Program units. Information on age, duration of diabetes, smoking status, alcohol consumption, and use of medication will be collected from each participant at baseline.

The presence of retinopathy will be assessed from chart reviews.

The presence of nephropathy will be assessed by dividing the UAE into three categories, as follows: normoalbuminuria, UAE < 30 mg/g Cr; microalbuminuria, 30–300 mg/g Cr; or macroalbuminuria, > 300 mg/g Cr.

Neuropathy will be defined based on the diagnostic criteria for diabetic polyneuropathy proposed by the Diabetic Neuropathy Study Group [16].

Macrovascular complications will be defined as the presence of previous cardiovascular disease, cerebrovascular disease, or arteriosclerosis obliterans, on the basis of clinical history or physical examination.

Changes in diabetic medication (number of drugs currently prescribed to the patient; dose of drugs; initiation of new medication during study period; initiation of injectable diabetic medication; initiation of insulin; number of medications stopped or changed during the study period) and changes in antihypertensive medication (number of drugs started and stopped during study period; dose of drugs; initiation of new medication during study period) will be recorded. We will exclude patients from the analysis who were newly prescribed or stopped thiazide diuretics and sodium glucose transporter 2 inhibitors during the study.

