### Exclusion criteria

Patients will be excluded from the study if they have any of the following exclusion criteria: history of or features indicative of an eating disorder; secondary hypertension or malignant hypertension; pregnant, breast-feeding, or planning to become pregnant within the next 6 months; myocardial infarction, cerebrovascular accident, or hospitalization for angina pectoris within the previous 6 months; change in antihypertensive medication and/or antidiabetic medication within the previous month; cardiac failure (grade II, III, or IV according to the New York Heart Association) [14]; atrial fibrillation or severe arrhythmia; advanced renal failure (serum creatinine greater than or equal to 2.0 mg/dL or patient currently on dialysis); life-threatening condition such as a malignant tumor; intercurrent serious infection; significant psychiatric disorder or diagnosed substance abuse; serious neurological disorder, including epilepsy; unable to change their diet (currently in a facility or using home delivery); or recruiting physician considers the patient to be unsuitable for the study for any other reason.

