### Allocation

All participants will be randomized to one of the two arms (intervention or control) in equal ratios, using permuted block randomization, with block sizes of ten. An independent researcher will draw lots to assign each participant to a group directly after obtaining the participant’s informed consent. Because of the nature of this study, it will not be possible to blind participants, physicians, or some of the researchers to the treatment allocation.

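### Excluding patients who start or stop a thiazide or SGLT2 inhibitor after randomisation contradicts the stated intention-to-treat analysis and can bias the comparison by an unknown amount in an unknown direction

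*Protocol article*

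**What the plan says.** The protocol article's Secondary outcomes section ends with a paragraph on recording changes in diabetic and antihypertensive medication. Its last sentence reads: "We will exclude patients from the analysis who were newly prescribed or stopped thiazide diuretics and sodium glucose transporter 2 inhibitors during the study". It does not restrict the rule to a secondary outcome, a per-protocol set or a sensitivity analysis.

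Statistical methods states, also without restriction: "We will use an intention-to-treat analysis". The same section adds "Multiple imputations will be applied if there are missing values" and "Factors and changes in factors that may influence sodium intake will be adjusted in multivariate models". Neither sentence mentions the excluded patients, and no modified intention-to-treat set is defined.

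Other sections bear on the point:
- Allocation: "it will not be possible to blind participants, physicians, or some of the researchers to the treatment allocation".
- Secondary outcomes: "The secondary outcomes will include body weight, hemoglobin A1c, blood pressure".
- Primary outcome: "daily salt intake will be measured using a spot morning urine sample", with intake calculated from urinary sodium and creatinine.
- Exclusion criteria: a "change in antihypertensive medication and/or antidiabetic medication within the previous month" bars entry. This covers the period before entry and does not limit changes during the 24 weeks of follow-up.

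**The concern.** Intention-to-treat keeps every randomised patient in the arm assigned. The exclusion rule removes some of them because of a prescribing event after assignment. An analyst holding both sentences must break one of them, and could make that choice with unblinded data in hand.

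The removed patients need not be a random subset. The drugs concerned are named in a paragraph on diabetic and antihypertensive medication, and blood pressure and HbA1c are trial outcomes. The Introduction links salt intake to blood pressure. Physicians know the allocation, and the regular physician gives the advice. Information during follow-up also differs: the intervention group is told its salt intake at later visits, while Table 1 shows the control group being told only at allocation. A drug change may therefore depend on the arm, on the outcome, or on both. If it does, the patients left in the two arms are no longer comparable through randomisation.

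The rule also costs patients, and the sample size allows for dropout only.

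**Working it through.** **1. The two rules side by side.** The exclusion is triggered by an event during the study, so it is post-randomisation by definition. It applies to the analysis without limit. The intention-to-treat statement is equally unlimited. If the section heading is taken to confine the exclusion to secondary outcomes, those outcomes still fall under the intention-to-treat statement. The conflict stands on either reading and needs no calculation.

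**2. The plan's own sample size.** Statistical methods gives a 1 g difference, two-sided 5%, 80% power, 90 per group, 10% dropout and 200 in total.
- Dropout step: 180 / 0.9 = 200. This reproduces.
- Number per group, by n = 2(1.960 + 0.842)² SD² / 1². The SD used is not stated. With the printed SDs, 1.6 gives 40.2 (41 per group) and 1.9 gives 56.7 (57 per group). Neither gives 90.
- Solving backwards from 90: SD = 1 / [2.802 × √(2/90)] = 2.39 by the normal approximation, or 2.38 by the t-test.

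The unexplained 90 is a separate matter. It matters here only because the power loss depends on which SD is right.

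**3. Power after exclusions.** From 100 per group, 10% dropout leaves 90. A further fraction e of completers excluded leaves 90(1 − e). No value of e is given, so 10% and 20% are assumptions. Two-sample t-test, 1 g difference, two-sided 5%:

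| Per group | SD 1.6 | SD 1.9 | SD 2.38 (implied) |
|---|---|---|---|
| 90 (e = 0) | 99% | 94% | 80% |
| 81 (e = 10%) | 98% | 91% | 76% |
| 72 (e = 20%) | 96% | 88% | 71% |

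**4. Bias, as an illustration.** Suppose a fraction e of an arm is excluded and those patients' change in salt intake averages D g/day above their arm mean. The retained mean then falls by D × e/(1 − e). The intervention-minus-control difference shifts by D × [e_c/(1 − e_c) − e_i/(1 − e_i)], taking the same D in both arms. A benefit is negative, so a positive shift hides benefit. All rates and values of D are assumed.
- 15% of controls and 5% of intervention patients: 0.176 − 0.053 = 0.124, so +0.12 g/day for D = 1 and +0.25 for D = 2.
- 20% and 5%: 0.250 − 0.053 = 0.197, so +0.20 and +0.39 g/day.
- 5% of controls and 15% of intervention patients: −0.12 and −0.25 g/day, which exaggerates benefit.
- D = 0 (exclusion unrelated to outcome): no shift.

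A milder case was simulated with SD 2.39 and a true 1 g effect. The same exclusion rule applied in both arms, with a 10% risk at the control mean and log-odds rising by 0.5 or 1 per SD of salt change. Exclusions came out at 10.9% of controls against 9.1% of intervention patients, and 13.4% against 9.6%. The estimated effect was 0.98 g and 0.92 g.

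**The case against.** **The rule has a reason.** Salt intake is inferred from spot urinary sodium and creatinine. If these drugs alter urinary sodium, which is presumably why they were singled out (the article does not say), a value taken after a drug change may not reflect intake. If drug changes also differ by arm, keeping such values puts arm-dependent measurement error into the primary endpoint, which is more than noise. This stands. It explains the rule and raises the price of dropping it, but it does not reconcile the rule with intention-to-treat. Dropping the patient altogether is also not the only way to handle an affected value.

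**The effect may be small.** Recent medication changes bar entry, and nothing in the article suggests that many patients will start or stop one of two drug classes in 24 weeks. The bias figures all rest on assumed rates. This also stands.

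**Two stronger readings are tempting.** A reader might infer that controls, with salt intake and blood pressure staying high, will be removed more often and a real benefit hidden. The article gives no rates by arm, and the rule covers stopping a drug as well as starting one, so patients who improve could be removed too. A reader might also infer that the trial would be underpowered. That follows only at the SD solved back from 90 per group. With either printed SD, power stays at 88% or more even after a further 20% exclusion.

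**An unseen analysis plan might settle it.** That would excuse missing detail, but here both rules are printed and they conflict.

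**Conclusion.** The contradiction is certain: the exclusion rule and the intention-to-treat statement cannot both be applied, and the article does not say which governs. It must be resolved because it decides who enters the primary comparison.

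The exclusion can bias the comparison, and no more than that can be said. In the scenarios above the shift ranges from nothing to about 0.4 g/day against a 1 g target. Those figures depend entirely on assumed exclusion rates and on how far excluded patients differ from the rest. The article supports neither a particular size nor a particular direction.

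The exclusions come on top of the 10% dropout allowance. With 20% of completers removed, power at 1 g is about 71%, 88% or 96% for an SD of 2.38, 1.9 or 1.6. A material loss is therefore possible but not established.

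**What to change.** Reconcile the Secondary outcomes and Statistical methods sections:

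- **Primary analysis:** all randomised patients, analysed as allocated, whatever medication changes occur.
- **Sensitivity analysis 1:** the thiazide/SGLT2-inhibitor exclusion as now written, labelled as such.
- **Sensitivity analysis 2:** all randomised patients, with salt-intake values after the drug change set to missing and multiply imputed.
- **Reporting:** the number of patients starting or stopping either drug class, by arm.

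The cost is a few sentences. Medication changes are already to be recorded and multiple imputation is already planned, so no new data are needed. The real downside is that any drug effect on urinary sodium, possibly different between arms, stays in the primary estimate. The two sensitivity analyses and the counts by arm are there to show whether it matters.

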### Statistical methods

A mixed model will be used to analyze the factors involved in sodium intake. Factors and changes in factors that may influence sodium intake will be adjusted in multivariate models. Subgroup analyses will be conducted stratified by age (< 65 years or ≥ 65 years), sex (male or female), body mass index (< 22%, or ≥ 22%), and hemoglobin A1c levels (< 7%, or ≥ 7%) to investigate the coherency of educational effect among subgroups. The secondary outcomes will be compared using separate regression models. The differences of values between the two groups with 95% confidence interval and a *p* value < 0.05 will also be presented. We will use an intention-to-treat analysis. JMP version 11.2.0 software (SAS Institute, Cary, NC, USA) will be used as the statistical software package for the analysis. All analyses will be two-sided, and *p* values < 0.05 will be considered statistically significant. Multiple imputations will be applied if there are missing values. In a previous study, it was shown that after patients with T2DM were given instructions on reducing salt intake, their salt intake declined from 10.3 ± 1.6 g to 9.3 ± 1.9 g per day [10]. Therefore, we have based our sample size calculation on the assumption that the intervention group will show a 1-g reduction in their daily salt intake, and that the salt intake in the control group will remain unchanged. With the two-sided significance level set at 5.0% and power set at 80%, the required sample size will be 90 participants in each group. Assuming a 10% dropout rate [17], a total of 200 participants will be required for both groups combined.

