**Methods:**

In this unblinded randomized controlled trial (RCT), a total of 200 patients, male or female, aged between 20 and 90 years, who have type 2 diabetes mellitus and consume excessive salt will be randomly assigned to two groups: an intervention group and a control group. In addition to being given routine treatment, participants in the intervention group will be given individual guidance on restricting their dietary salt intake by a physician upon enrollment. The control group will only be given routine treatment. Participants will be followed up for 24 weeks. The primary outcome will be dietary salt intake, which will be assessed at baseline and at 8, 16, and 24 weeks. The secondary outcomes, including body weight, body mass index, hemoglobin A1c level, blood pressure, blood glucose level, serum lipid profile, and urinary albumin excretion level, will be assessed at baseline and at 8, 16, and 24 weeks.

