## Methods

### Study design

The study will be an unblinded RCT aimed at testing whether instructions on dietary salt restriction provided by physicians during outpatient visits is effective in reducing salt intake in patients with type T2DM who have an excessive salt intake. A total of 200 patients with T2DM and excessive salt intake (150 from the Hospital of the Kyoto Prefectural University of Medicine, 50 from Kyoto First Red Cross Hospital according to the proportion of outpatients) will be randomly assigned to an intervention group or a control group, using permuted block randomization, with block sizes of ten. Spot morning urine tests will be performed, and the results will be used to estimate their salt intake. The primary outcome will be the change in daily salt intake between baseline and 24 weeks. Each participant will be enrolled for 24 weeks from randomization to the final follow-up assessment and will visit every 8 weeks (Fig. 1).

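### The primary outcome is stated in two ways, and the salt-intake model neither fixes the randomised 24-week contrast nor keeps out covariates measured after randomisation

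*Protocol article*

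**What the plan says.** The protocol article states the primary outcome in three places.

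- Study design: "The primary outcome will be the change in daily salt intake between baseline and 24 weeks".
- Abstract, Methods: "The primary outcome will be dietary salt intake, which will be assessed at baseline and at 8, 16, and 24 weeks".
- Primary outcome: "The primary outcome will be dietary salt intake and will be assessed at baseline and at 8, 16, and 24 weeks".

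Statistical methods gives one model for salt intake: "A mixed model will be used to analyze the factors involved in sodium intake". The next sentence sets the adjustment: "Factors and changes in factors that may influence sodium intake will be adjusted in multivariate models". Later, after the sentence on secondary outcomes, the section promises "The differences of values between the two groups with 95% confidence interval", without naming an outcome or a visit. It also states intention-to-treat analysis and two-sided tests at 5%.

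The sample size rests on this premise: "the intervention group will show a 1-g reduction in their daily salt intake, and that the salt intake in the control group will remain unchanged". The section then concludes: "With the two-sided significance level set at 5.0% and power set at 80%, the required sample size will be 90 participants in each group". The SDs quoted from the previous study are 1.6 g before and 1.9 g after instruction. The section does not say which SD, or what correlation, lies behind the figure of 90.

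**The concern.** A change to one fixed visit and a level followed over four visits, one of them before treatment, are different outcomes and lead to different tests. The analysis section would normally show which is meant. Here it describes a model of factors and does not name the comparison that was randomised. In an unblinded trial, this leaves the 8-, 16- and 24-week differences, and an average over visits, all available as the headline result at p < 0.05.

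The adjustment is a second problem. Changes in factors during follow-up, for example in body weight or blood pressure, come after randomisation, and dietary advice may move them. A group coefficient conditioned on them need not be the total effect of the advice, which is what the trial aims to estimate.

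Efficiency is also at stake. If the change score is taken literally, the full noise of a single spot-urine baseline enters the outcome. Using baseline as a covariate removes only what baseline predicts.

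**Working it through.** **1. The definitions side by side.** Study design fixes a measure (change) and a time (24 weeks). The abstract and the Primary outcome section fix neither. Statistical methods names no group term, visit or baseline term for salt intake, so it does not choose between them.

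**2. The plan's sample size.** For 80% power, two-sided 5%, 1:1: n per group = 2(1.960 + 0.842)² × SD²/d² = 15.70 × SD²/d². With d = 1 g:

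- SD 1.6: n = 41
- SD 1.756 (pooled 1.6 and 1.9): n = 49
- SD 1.9: n = 57

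None gives 90. Solving for the SD: √(90/15.70) = 2.39 g. A change score has SD = √(1.6² + 1.9² − 2r × 1.6 × 1.9), so r = (2.56 + 3.61 − 2.394²)/6.08 = 0.07, or 0.08 with the t distribution. The figure 90 also follows from d = 0.8 g with SD 1.9 (89 by the normal formula, 90 by t), although Statistical methods says 1 g. The dropout step reproduces: 180/0.9 = 200.

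**3. Change score against baseline-adjusted 24-week value.** The inputs are SDs of 1.6 and 1.9 g and 90 per group (Statistical methods), and effects of 1 g (Statistical methods) and 0.7 g (the Introduction's 6-month figure for the cited study). The correlation r is an assumption, shown over a range. The adjusted SD is 1.9 × √(1 − r²). Power is from the two-sample t-test.

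| r | SD change | SD adjusted | Power at 1 g, change v adjusted | Power at 0.7 g, change v adjusted |
|---|---|---|---|---|
| 0.08 | 2.38 | 1.89 | 80% v 94% | 50% v 69% |
| 0.3 | 2.09 | 1.81 | 89% v 96% | 61% v 73% |
| 0.5 | 1.77 | 1.65 | 96.5% v 98% | 75% v 81% |
| 0.7 | 1.38 | 1.36 | 99.8% v 99.8% | 92% v 93% |

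At r = 0.08 the variance is 37% lower (1 − 1.894²/2.384²). By r = 0.7 the two approaches are practically the same.

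**4. Cost of leaving the visit open.** With no true effect and equal correlation between visits (an assumption), simulation gives the chance that at least one of the 8-, 16- and 24-week differences reaches p < 0.05. It is about 14% at correlation 0.08, 12.5% at 0.5 and 11% at 0.7, against the nominal 5%. This is the exposure if the visit were chosen after seeing the data. Nothing in the protocol says that it will be.

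**The case against.** The strongest defence is that the texts can be read together. Study design gives the measure and the time point, while the abstract and the Primary outcome section name the variable and its measurement schedule. No section makes 8 weeks, 16 weeks or an average the primary contrast. Whether baseline is an outcome or a covariate, and whether group by visit is fitted, are details often left to an analysis plan, and none is shown. This has weight: it makes 24 weeks the likely intention. It does not remove the inconsistency, because the section headed as the primary outcome drops the time point and the model sentence does not restore it. The adjustment for changes in factors is something the article states, so it is not a detail left out.

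Several stronger readings are tempting and are not supported.

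- A reader might infer that no test of the randomised groups is planned. The section does promise between-group differences with confidence intervals, and a mixed model can yield the 24-week contrast. The fault is that the contrast is not fixed.
- A reader might infer that the plan clearly loses power. The stated model is too loosely specified for its power to be computed. The comparison above is with a simple change score only, and r is not given.
- A reader might infer that a group effect averaged over all four visits dilutes 1 g to (0 + 1 + 1 + 1)/4 = 0.75 g. The plan does not state such an analysis.
- A reader might take the separate regression models for secondary outcomes to be unadjusted. The text does not say so.

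**Conclusion.** The point stands in this form: the primary outcome is inconsistently stated, the salt-intake model does not fix the 24-week group contrast, and the stated adjustment admits variables that the intervention may affect.

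The power argument is secondary and conditional. Baseline adjustment is at least as powerful as a change score across the range examined. At the planned 1 g the gain is about 14 percentage points at r = 0.08, 6 to 7 at 0.3, under 2 at 0.5 and practically nil at 0.7. At 0.7 g it is about 19, 12, 6 and 1 points. The largest gains apply only if 90 came from a change-score calculation at 1 g with the printed SDs. That is an inference, since 0.8 g with SD 1.9 gives the same number. All these figures assume SDs of 1.6 and 1.9 g and 90 analysed per group.

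**What to change.** State one primary estimand in the abstract, Study design, Primary outcome and Statistical methods: the between-group difference in daily salt intake at 24 weeks. Estimate it from a mixed model of the 8-, 16- and 24-week values with group, visit, group by visit, and baseline salt intake as covariate. With baseline in the model, analysing the values or their changes from baseline gives the same group difference, so the intention in Study design is kept.

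Declare the week 8 and week 16 contrasts secondary. Keep every covariate measured after randomisation out of the primary model. The analysis of factors and their changes can remain as a separate, exploratory analysis. State the SD and correlation behind the figure of 90, and show power over a range of r.

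The cost is wording only: the baseline value is already collected, and no new data or visits are needed.
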